### Measures

#### Sample Characteristics

Participants will be asked to provide demographic characteristics, such as age, gender, race, ethnicity, marital status, and education level. We will also abstract from the medical record OSA history (severity and PAP settings). Comorbidities will be summarized by the Self-Administered Comorbidity questionnaire (convergent validity with Charlson Comorbidity index *r*=0.55) [23]. Participants' overnight oxygen desaturation, based on clinical overnight oximetry, will be summarized by the amount of time spent at various oxygen saturation levels.

#### Primary Outcome Measure

The primary outcome measure will be the change in PAP adherence (average minutes per night over a 7-day period) from T1 to T3. PAP adherence, defined as the use of the device for 4 or more hours per night on 70% of nights during a consecutive 30-day period [20], is measured continuously and is recorded by the participant’s PAP machine and transmitted to the participant’s PAP account (eg, AirView and Care Orchestrator) through a cellular modem that is embedded in the device [24]. PAP devices can distinguish between periods when the mask is on versus off the face (by detecting flow).

#### Secondary Outcome Measures

Additional PAP adherence metrics will be abstracted from the participant’s PAP modem report: Percentage of days used for 4 or more hours, number of days used out of 7 days, and average residual apnea-hypopnea index on therapy.

Participant acceptability will be assessed [25]. We will review the data and evaluate the proportion of nights participants used the wearable overall and while on treatment to ascertain feasibility and acceptability of using a wearable to collect SpO_2_ data. We will further assess intervention feasibility, acceptability, and appropriateness with items developed by Weiner et al [25]. The postprogram survey will be followed by an interview with patients about their experience using the wearable with treatment, including opinions about the wearable program and intention to continue using the wearable.

#### Other Measures

Sleep disturbance and sleep-related impairment will be measured by the 8-item Patient-Reported Outcomes Measurement Information System (PROMIS) Sleep Disturbance and 8-item Sleep-Related Impairment [26]. Scores are presented as *t* scores, with an average of 50 and SD of 10. Scores >60 are considered elevated. Internal consistency has previously been very high (Cronbach α>0.94) [27].

Hypersomnolence will be assessed with the 8-item Epworth Sleepiness Scale [28]. Score ranges from 0 to 24 (internal consistency Cronbach α=0.82) [29].

Determinants of PAP compliance subscales (self-efficacy, 5 items; knowledge, 12 items) and transtheoretical model (decision balance, 11 items; stages of change, 1 item), chosen from constructs of social cognitive theory, will measure factors that are commonly associated with PAP use (subscale Cronbach α=0.66-0.93) [21].

Graph literacy will be evaluated using a 4-item Short Graph Literacy Scale [30] that presents data in the form of a chart and queries the respondent’s comprehension, with the number of correct answers out of 4 indicating graph literacy. This short scale has convergent validity with both the Long Graph Literacy Scale (*r*=0.90) and a detailed verbal query of how well the participant comprehended the graph (*r*=0.44).

The impact of OSA on biopsychosocial aspects (eg, mood and/or psychosocial outcomes) will be assessed using the Symptoms, Tiredness, Alertness, Mood, and Psychosocial questionnaire [31]. It is a 12-item questionnaire that is scored on a 6-point scale (internal consistency Cronbach α=0.91).

### Statistical Analysis

An intention-to-treat approach will be used. Demographic and clinical characteristics, as well as all outcome measures at baseline, will be summarized using descriptive statistics by study arm to assess baseline comparability. If the distribution of the continuous variable is skewed, an appropriate variable transformation will be made before the comparison. Multiple imputation will be implemented to account for missing data using software for regression models developed by Belin et al [32], Liu et al [33], and Schafer [34].

Changes in sleep-related outcome measures will be analyzed to assess the “success” (effect) of the wearable intervention. The primary sleep-related outcome is change in average minutes per night of PAP use from T1 to T3. Our primary hypothesis is that the proposed intervention program will improve PAP adherence among participants who receive the program immediately compared to a waitlist control group. The primary analysis will be a comparison of mean change in PAP use between the immediate intervention group and the waitlist control group using a 2-sample, 2-sided *t* test (unadjusted). Next, we will construct an analysis of covariance regression model that includes baseline PAP adherence score, study arm (intervention vs control), demographic characteristics (eg, age), and preselected clinical characteristics (eg, determinants of PAP compliance score, OSA severity, and PAP setting) to examine whether the effect of the wearable intervention on PAP adherence, where the change score is the primary outcome, is significant. Because this is a single-site pilot, we have no plans to conduct any interim analyses that would be used to determine termination of trial.

Secondary analyses will compare secondary outcomes, such as the percentage of days used for ≥4 hours out of 28 days and the percentage of days used out of 28 days, between study arms. These comparisons will use generalized linear mixed-effects models with appropriate link functions, such as logit for binary outcomes and log for count outcomes. Each regression model will include the fixed effects of interest (study arm, time, and a 2-way study arm-by-time interaction term) and participant-level random effects to account for dependency of repeated observation within participants. Similar to the primary analysis, adjusted analyses of secondary outcomes with preselected factors will be performed. In addition, a generalized linear mixed-effects model will be used to compare change scores before and after the wearable intervention within the waitlist control group to estimate whether the difference in change scores before and after is significant (secondary hypothesis). This analysis will include the PAP adherence measurements from T1 to T5 for all the waitlist control participants. A similar modeling approach will be used to evaluate whether the effect of the 28-day wearable intervention is maintained at the end of the study (exploratory analysis).

Participant acceptability will be measured and analyzed to assess acceptability. We will summarize acceptability measures (frequency, mean, etc). For interview data, we will summarize interview content thematically using Veterans Affairs (VA)–approved qualitative data analysis software (eg, ATLAS.ti) and identify ways to improve the protocol for a future full-scale trial.

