**Methods:**

This is a single-blinded randomized controlled trial. We will randomize 50 individuals with a history of OSA, who receive care from a Department of Veterans Affairs medical center in the Los Angeles area and are nonadherent to prescribed PAP therapy, into either an immediate intervention group or a waitlist control group. During a 28-day intervention, the participants will wear a study-provided consumer wearable device and complete a weekly survey about their OSA symptoms. A report that summarizes consumer wearable–provided oxygen saturation values, PAP use derived from modem data, and patient-reported OSA symptoms will be prepared weekly and shared with the patient. The immediate intervention group will begin intervention immediately after randomization (T1). Assessments will occur at week 5 (T3; 1 week after treatment for the immediate intervention group and repeat baseline for the waitlist control group) and week 11 (T5; follow-up for the immediate intervention group and 1 week after treatment for the waitlist control group). The primary outcome will be the change in 7-day PAP adherence (average minutes per night) from T1 to T3. The primary analysis will be a comparison of the primary outcome between the immediate intervention and the waitlist control groups (intention-to-treat design), using a 2-sample, 2-sided *t* test on change scores (unadjusted).

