#### Assessments

##### Baseline Assessment

Participants in both arms will undergo a baseline assessment (T1 for the immediate intervention group; T3 for the waitlist control group), where current 7-day and 30-day PAP adherence will be collected from modem data. One-night oximetry using a United States Food and Drug Administration–approved wrist-worn pulse oximeter (Nonin) will be conducted. Other measures such as determinants of PAP compliance (ie, self-efficacy, knowledge, stages of change, and decisional balance index) [21], sleep disturbance, sleep quality, daytime function, comorbidities, and health literacy will be collected through an electronic survey using the Qualtrics platform. A baseline assessment appointment with a research team member will be conducted, where the research team member will review the survey and administer any items that were unintentionally left incomplete.

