### Power and Sample Size Considerations

A sample size of 25 participants per study arm will provide at least 80% power to detect a standardized effect size (Cohen *d*) of 0.72 using a 2-group test with a .05 two-sided significance when comparing mean changes in primary outcome between study arms. We anticipate a relatively larger effect size because the study time point is in a shorter time frame after treatment. The effect size estimated from this pilot study will be used to plan a future full-scale, multiyear trial.

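### The primary test is an unadjusted t test on change scores, with the baseline-adjusted model run only afterwards; making adjustment for T1 use primary would cost one degree of freedom and would usually gain precision

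*Protocol article*

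**What the plan says.** Under Primary Outcome Measure, the outcome is the "change in PAP adherence (average minutes per night over a 7-day period) from T1 to T3". Statistical Analysis then states: "The primary analysis will be a comparison of mean change in PAP use between the immediate intervention group and the waitlist control group". The Methods paragraph of the Abstract gives the same test, "using a 2-sample, 2-sided *t* test on change scores (unadjusted".

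The sentence after the primary test in Statistical Analysis brings in baseline adjustment: "Next, we will construct an analysis of covariance regression model that includes baseline PAP adherence score, study arm (intervention vs control), demographic characteristics" and preselected clinical characteristics, with the change score as the response. This model is a follow-on to the t test.

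Under Baseline Assessment, "current 7-day and 30-day PAP adherence will be collected from modem data". Participant Timeline places the T1 assessment before randomization, and T1 use is in any case part of the change score in both arms. Randomization describes permuted blocks and mentions no stratification on baseline use. Power and Sample Size Considerations refers to a two-group comparison of mean changes: "A sample size of 25 participants per study arm will provide at least 80% power to detect a standardized effect size" of 0.72, two-sided at .05. It adds that the pilot's effect estimate will be used to plan a full-scale trial.

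**The concern.** A change score is a baseline adjustment whose coefficient is set to 1 in advance. ANCOVA estimates that coefficient. If people with higher T1 use keep only part of that excess at T3, the true slope is below 1. The change score then takes off too much baseline, adds variance, and moves the estimate against whichever arm happened to start with higher use. A slope below 1 is plausible here, because each 7-night mean carries night-to-night noise, but the documents do not give it.

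Two things are at stake: the power of the one test that carries the primary conclusion, and the precision of the estimate that is meant to size the next trial. The better-placed model is already planned and its key covariate is already collected, so the question is which analysis should be primary.

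**Working it through.** **Inputs.** From the protocol: 25 per arm, d = 0.72, two-sided alpha 0.05, t test on T1–T3 change. Assumed, because the documents give no value: the T1–T3 correlation rho (range 0.3 to 0.9) and, at first, equal SDs at T1 and T3. The effect d is taken in units of the SD of change, since the protocol frames it as a comparison of mean changes.

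**1. The protocol's own figure.** Noncentrality = 0.72 × √(25/2) = 2.55, with 48 degrees of freedom. Two-sided power is 70.3% by the noncentral t (72.1% by the normal approximation), not at least 80%. A two-sided test needs 32 per arm, or d = 0.81 at 25 per arm, for 80%. Only a one-sided 0.05 test gives about 80% (80.6%). That shortfall is a separate matter; here 70.3% is the starting point.

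**2. Large-sample variance.** Let s1 and s3 be the SDs at T1 and T3.
- Change score: s1² + s3² − 2·rho·s1·s3
- ANCOVA: s3²(1 − rho²)
- Difference: (s1 − rho·s3)², which is never negative and is zero only when the slope rho·s3/s1 equals 1.

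With s1 = s3 the ratio ANCOVA/change is (1 − rho²)/(2(1 − rho)) = (1 + rho)/2.

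**3. Power at 25 per arm.** Estimating the slope costs one degree of freedom (48 to 47) and inflates the variance by 1 + 1/(2n − 4) = 1 + 1/46 = 1.022. The effective d is 0.72/√(ratio × 1.022). At rho 0.5 this is 0.72/√(0.75 × 1.022) = 0.82.

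| Assumed rho | (1 + rho)/2 | × 1.022 | ANCOVA power | n per arm for 80% |
|---|---|---|---|---|
| 0.3 | 0.65 | 0.66 | 86.4% | 22 |
| 0.5 | 0.75 | 0.77 | 81.3% | 25 |
| 0.6 | 0.80 | 0.82 | 78.7% | 26 |
| 0.7 | 0.85 | 0.87 | 76.3% | 28 |
| 0.8 | 0.90 | 0.92 | 73.9% | 29 |
| 0.9 | 0.95 | 0.97 | 71.6% | 31 |

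The t test stays at 70.3% throughout and needs 32 per arm. A simulation of 40,000 trials at each of rho 0.3, 0.5, 0.7, 0.8 and 0.9 gave variance ratios of 0.67, 0.77, 0.87, 0.92 and 0.97, and ANCOVA powers within half a percentage point of the table.

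**4. Unequal SDs.** If the T3 SD is 1.25 times the T1 SD, the large-sample ratio is 0.89 at rho 0.5, 0.98 at 0.7 and 1.00 at 0.8 (slope 0.8 × 1.25 = 1). At a slope of exactly 1, ANCOVA pays the 1.022 factor for nothing, a loss of about 2% in variance.

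**5. Chance imbalance.** The standard error of the baseline difference is √(2/25) = 0.28 SD. Given an imbalance of that size, the change-score estimate shifts by (1 − rho) × 0.28 SD against the arm with higher baseline use: 0.20, 0.14, 0.08 and 0.06 SD at rho 0.3, 0.5, 0.7 and 0.8. In change-score SD units (SD of change = √(2(1 − rho)) SD) the shift is 0.14 at rho 0.5 and 0.09 at rho 0.8, which is 0.14/0.72 = 20% and 0.09/0.72 = 12% of the target effect.

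**The case against.** The strongest reply is that nothing here is wrong. The t test is prespecified, stated consistently, valid, and unbiased over randomizations. The baseline-adjusted model is planned in the next sentence, and modelling change or T3 gives the same arm effect, so the adjusted estimate will be produced anyway. The size of the gain rests on an unstated rho and may be small. All of that stands. It does not make the choice a mere label: the primary test carries the conclusion, and the pilot's estimate feeds the next trial.

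A reader might infer more than the documents support:
- *That chance imbalance is left uncorrected.* It is not. The change score corrects it with the wrong slope when the true slope differs from 1. The shift in step 5 is conditional on the imbalance and averages to zero over randomizations.
- *That selecting low users biases the comparison through regression to the mean.* Both randomized arms enter under the same rule, so the expected drift is the same in each and cancels.
- *That the covariate list of the planned ANCOVA is a defect.* The protocol calls the clinical covariates preselected, and an article commonly leaves the full list to an analysis plan.
- *That a 30-day baseline mean would add a known further gain.* Baseline Assessment mentions 30-day adherence, but Primary Outcome Measure defines adherence over 30 days by a threshold. A 30-day mean in minutes is not explicitly stated, and no variance components are given to size its effect.
- *That ANCOVA rescues the stated 80%.* It reaches 80% only at rho of about 0.5 or below with equal SDs, and the power paragraph does not invoke it.

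**Conclusion.** The point holds as a question of efficiency and of conditional accuracy, not as an error of validity. Ranking the unadjusted change-score test above the baseline-adjusted model gives up about 11 percentage points of power at rho 0.5, 6 at 0.7 and 4 at 0.8, and close to none when the slope approaches 1. These figures assume 25 per arm, equal T1 and T3 SDs, d in change-score SD units and T1 use as the only covariate. A larger SD at T3 can shrink the gain. The direction does not depend on the assumed rho: in large samples ANCOVA cannot do worse, and at this sample size its worst case is about 2% extra variance. The change is well worth making but is not essential to a valid trial.

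**What to change.** In Statistical Analysis and in the Abstract, define the primary analysis as a linear model of T3 average minutes per night on study arm and T1 average minutes per night, both over 7 days. Using the T1–T3 change as the response gives the same arm effect, so the primary outcome as defined can stay. Name T1 use as the only covariate in this model. Keep the unadjusted t test as a sensitivity analysis and the planned ANCOVA with the longer covariate list as secondary. The power paragraph should then name this analysis and state the correlation it assumes.

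The cost is a wording change and one degree of freedom, with no new data and no further recruitment. The change should be made before outcomes are compared by arm.

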### Power and Sample Size Considerations

A sample size of 25 participants per study arm will provide at least 80% power to detect a standardized effect size (Cohen *d*) of 0.72 using a 2-group test with a .05 two-sided significance when comparing mean changes in primary outcome between study arms. We anticipate a relatively larger effect size because the study time point is in a shorter time frame after treatment. The effect size estimated from this pilot study will be used to plan a future full-scale, multiyear trial.

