## Methods

### Study Design

This study is a randomized parallel 2-group waitlist-controlled trial with 1:1 allocation evaluating the efficacy of a consumer wearable–augmented self-monitoring program on PAP adherence compared to a standard self-monitoring program on PAP adherence among patients with OSA prescribed PAP therapy. In addition, following the primary end point, the control group will crossover to the intervention condition and be compared to their time in the control condition (ie, single-group nonrandomized crossover design). The SPIRIT (Standard Protocol Items: Recommendations for Interventional Trials) 2013 statement was used to report standard protocol items for clinical trials [19].

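### The stated power does not follow from its inputs: 25 per arm with a two-sided .05 t test gives 70% power at d = 0.72, and 80% power needs d = 0.81

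*Protocol article*

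**What the plan says.** The section Power and Sample Size Considerations puts sample size, effect size, significance level, sidedness and power into one statement: "A sample size of 25 participants per study arm will provide at least 80% power to detect a standardized effect size". The effect is set at d = 0.72, and the power is that for comparing mean change between the arms, "using a 2-group test with a .05 two-sided significance". The section explains the large effect by the short interval between treatment and assessment.

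The rest of the article fixes the remaining inputs:

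- **Total size.** Abstract, Methods: "We will randomize 50 individuals with a history of OSA".
- **Allocation.** Study Design: a "randomized parallel 2-group waitlist-controlled trial with 1:1 allocation".
- **Primary test.** Statistical Analysis: "The primary analysis will be a comparison of mean change in PAP use between the immediate intervention group and the waitlist control group", by an unadjusted two-sample, two-sided t test. The abstract says the same.
- **Covariate adjustment.** An analysis of covariance with baseline adherence and other covariates is planned as a further step after the t test. The power statement does not refer to it and gives no baseline correlation.
- **Interim looks.** None that would lead to early termination, so the significance level is not split.

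**The concern.** The effect is standardized, so no standard deviation has to be assumed. Power is then fully determined by n, d, the significance level and sidedness, and all four are stated. An effect of 0.72 with 25 per arm looks too small for 80% power in a two-sided test at .05.

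The article sets a primary efficacy hypothesis and tests it formally. If the power is overstated, the chance of missing an effect of the planned size is higher than readers are told, and a non-significant result would be given more weight than it deserves. The article also says the pilot will inform a full-scale trial. The pilot's effect estimate is not affected by this error, but the same calculation carried forward would undersize that trial.

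**Working it through.** **Inputs.** n = 25 per arm, d = 0.72, significance level .05 two-sided, claimed power at least 80% (all from Power and Sample Size Considerations); 1:1 allocation (Study Design); unadjusted two-sample t test on change scores (Abstract; Statistical Analysis).

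**Step 1. Power under the stated inputs.**

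- Degrees of freedom: 2 × 25 − 2 = 48.
- Noncentrality: d × √(n/2) = 0.72 × √12.5 = 2.546.
- Exact noncentral t, two-sided .05: power = **70.3%**, so the type II error is 29.7%.
- Normal approximation: Φ(2.546 − 1.960) = Φ(0.586) = 72.1%.

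The claimed figure is not reproduced. The shortfall is 8 to 10 percentage points, too large for rounding or a difference in software.

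**Step 2. Effect detectable with 80% power at 25 per arm.**

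- Normal approximation: (1.960 + 0.842) × √(2/25) = 2.802 × 0.2828 = 0.792.
- Exact: **d = 0.809**.

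**Step 3. Sample size for 80% power at d = 0.72, two-sided.**

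| n per arm | Exact power at d = 0.72 | Detectable d at 80% power |
|---|---|---|
| 25 | 70.3% | 0.809 |
| 30 | 78.3% | 0.736 |
| 31 | 79.6% | 0.723 |
| 32 | 80.9% | 0.711 |

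The exact solution is 31.27, so 32 per arm (64 in total).

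**Step 4. Where could 0.72 come from?**

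| Variant, 25 per arm | Power at d = 0.72 |
|---|---|
| One-sided .05 t test | 80.6% (detectable d = 0.713) |
| Two-sided .10 t test | 80.6% |
| Wilcoxon test, two-sided .05 (efficiency 0.955) | 68.3% |
| One-sample or paired test, n = 25 | 93.2% |

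The first two match the claim but contradict the stated two-sided .05 level. The Wilcoxon test falls short, and the one-sample or paired test is not a comparison between arms. The third step offers another possibility: 0.72 is the rounded detectable effect for 31 per arm, so it could have come from a different sample size. The article does not allow a choice between these explanations.

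**Step 5. Sensitivity to lost information.** The article gives no loss rate for the primary outcome. The rates below are assumptions.

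| Evaluable per arm (assumed loss) | Power at d = 0.72 | Detectable d at 80% power |
|---|---|---|
| 24 (4%) | 68.5% | 0.826 |
| 22 (12%) | 64.5% | 0.865 |
| 20 (20%) | 60.2% | 0.909 |

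**The case against.** Four points can be made for the plan.

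**Covariate adjustment could recover the power.** With equal variances at T1 and T3 and correlation ρ between them, adjusting for baseline reduces the residual variance to (1 + ρ)/2 of the variance of the change score. The detectable effect, in SDs of change, becomes 0.809 × √((1 + ρ)/2): 0.65 at ρ = 0.3, 0.70 at ρ = 0.5 and 0.75 at ρ = 0.7. It is at or below 0.72 when (1 + ρ)/2 ≤ (0.72/0.809)² = 0.792, that is, for ρ up to about 0.58. So a one-sided test is not the only route to the stated figure. This does not rescue the sentence, which concerns a two-group comparison of mean changes. The primary test is unadjusted, the covariance model comes after it, and no correlation is stated.

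**Attrition may be small.** PAP use is sent by modem and abstracted whether or not the participant wears the watch or views the reports, and multiple imputation is planned. That is fair: stopping the program need not mean a missing outcome. Imputation does not, however, generally restore the information lost when an outcome is missing. This part of the point is secondary and rests on assumed rates.

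**This is a pilot.** No decision rule depends on the t test, and feasibility and acceptability are also aims. That limits the consequence but does not make the figure correct, since the article chose to state a formal power claim for a formal primary test.

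**A fuller document may contain the details.** It cannot reconcile this statement. The stated n, d, level, sidedness and power contradict one another for the named test.

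**Conclusion.** The concern holds. Under the article's own inputs, power at d = 0.72 is 70.3%, not at least 80%, and the effect detectable with 80% power is d = 0.81. The type II error at the planned effect is 29.7%, about half as large again as the 20% implied.

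The result rests only on stated inputs and the usual t-test conditions (normal change scores, equal variances), with all 50 participants contributing full information. The more favourable normal approximation also falls short. That the claim came from a one-sided calculation is an inference, and the conclusion does not depend on it. The power statement must be corrected because it describes the primary comparison wrongly; the pilot design remains usable at its planned size.

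**What to change.** Replace the power sentence, leaving the sample size as it is:

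> With 25 participants per arm, a two-sided .05 two-sample t test on change scores has 80% power to detect d = 0.81, and 70% power at d = 0.72, assuming complete outcome data.

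If some loss of outcome information is expected, state the rate and the detectable effect at the resulting number. If a baseline-adjusted model is made primary, give the detectable effect under that model together with the assumed T1–T3 correlation (for example, 0.70 SD of change at an assumed correlation of 0.5) and the basis for that correlation. Raising the sample to 32 per arm would make the present claim true, but it is not needed to correct the text.

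The cost is one sentence and a less favourable figure. No extra participants are required, and the analysis and trial conduct do not change.
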